#### Power Analysis

We use simulations to evaluate statistical power for a two-sided test (α=.05). Our analysis will be based on outcomes for approximately 7200 operations over 2 years from 36 surgeons (approximately 100 operations per surgeon) at six hospitals. We estimate having approximately 98% power in detecting an odds ratio of 0.85 per one unit (standardized) increase in a surgeon’s technical skills for the rate of adverse events.

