#### Clinical Complications

We will calculate each surgeon’s adverse event rate for the previous 2 years using each hospital’s Society of Thoracic Surgeons (STS) data.

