### Aim 1: Investigate the Relationship Between Peer-Rater Assessments of a Surgeon’s Technical Skills and Variability in Risk-Adjusted Patient Adverse Events

#### Approach

We will conduct peer-reviewer assessments of recorded CABG operations at six MPOG hospitals (representing 36 surgeons) to associate technical skills with major adverse events.

Each surgical operation will be divided (using our video segmentation protocol) into prespecified phases containing the most critical operative portions. The DCC will distribute video segments for surgeon assessment via our HIPAA-compliant assessment platform that will provide assessors with a view of the operative field (from Cam SF, Figure 2). Surgeon assessors will provide domain-specific and overall summary judgements (using a modified OSATS taxonomy). Twenty percent of segments will be resubmitted for review to test assessor reliability. We will associate the average assessments with the adjusted risk of major morbidity and mortality over the prior 2 years for each surgeon.

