#### Analytical Plan

We will use linear mixed effect models to model assessments of surgical procedures where assessors and surgeons are included as random effects. We will quantify variation in peer-assessor assessments of a surgeon’s technical skills and use the intraclass correlation coefficient to measure interassessor reliability. We will use predictions of each surgeon’s technical skills from the linear mixed effect models as summary measures of a surgeon’s technical skills in subsequent analyses. Generalized linear mixed effect models with a logit link will then be used to associate a surgeon’s technical skills with our composite outcome. We will model surgeons and hospitals as random effects, accounting for the nesting structure of the data (ie, patients nested within surgeons and hospitals). We will adjust for patient and surgeon factors by including them as fixed effects in the models. The factors of interest are summary measures of a surgeon’s technical skills, which are included as surgeon-level explanatory variables. We will consider the overall assessments of a surgeon’s technical skills, averaged across three assessors and each domain individually.

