#### Power Analysis

The power analysis is based on approximately 7200 cases across 36 surgeons from six hospitals. As surgeon’s nontechnical practices are considered a surgeon-level variable, there will be sufficient power in detecting the same effect sizes as reported in aim 1.

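### The Aim 1 power statement gives two sample sizes that differ by a factor of two (36 surgeons at about 100 operations is 3600, not the stated total of 7200), and the 98% power, which Aim 2 also relies on, depends on which was simulated.

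*Protocol article*

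**What the plan says.** The Power Analysis under Aim 1 (Protocol article) describes a simulation-based, two-sided calculation at the 5% level, using "approximately 7200 operations over 2 years from 36 surgeons (approximately 100 operations per surgeon) at six hospitals". Its result is: "We estimate having approximately 98% power in detecting an odds ratio of 0.85 per one unit (standardized) increase" in surgeon technical skill.

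The Power Analysis under Aim 2 rests on "approximately 7200 cases across 36 surgeons from six hospitals" and claims sufficient power for the same effect sizes as Aim 1. It does not repeat the per-surgeon count.

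Two other statements bear on the calculation. The Clinical Complications section takes each surgeon's "adverse event rate for the previous 2 years", so the outcome window is 2 years. The Aim 1 Analytical Plan states: "We will model surgeons and hospitals as random effects", with skill entered as a surgeon-level explanatory variable. The power sections give no event rate. The only rate in the article is the 35% of CABG patients with major adverse events, in the Introduction.

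**The concern.** A total, a number of surgeons and a number of operations per surgeon appear in one sentence, and the third does not follow from the first two. The word approximately cannot cover a factor of two. The only period named in that sentence is 2 years, so a reader who takes it literally gets 100 operations per surgeon over 2 years and a total of 3600.

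This is more than a slip in presentation, because the 98% is the only stated power figure for both association aims. Skill varies between surgeons, not between patients. Power therefore depends on 36 surgeons, on how precisely each surgeon's event rate is estimated (which depends on operations per surgeon), and on the between-surgeon variation left after adjustment. A reader who does not know whether 100 or 200 operations per surgeon were simulated cannot tell which design the 98% describes.

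**Working it through.** **Inputs from the article:** 36 surgeons; 7200 operations; about 100 operations per surgeon; 2 years; two-sided α = 0.05; odds ratio 0.85 per SD of skill, so β = ln 0.85 = −0.1625; event rate p = 35% (Introduction).

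**Assumed inputs:** event rates of 15% and 20%, and the residual surgeon SD s on the logit scale, shown as a range.

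**Step 1. The count.**
- As printed: 36 × 100 = 3600.
- From the total: 7200 / 36 = 200 per surgeon over 2 years.
- If 100 is a yearly volume: 36 × 100 × 2 = 7200, which reproduces the total exactly.

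**Step 2. The plan's 98%.** It cannot be reproduced from the article, because the event rate and variance components that were simulated are not given. One can ask what it requires. With m operations per surgeon,

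Var(β̂) = [s² + 1/(m p(1−p))] / 36, and power = Φ(|β|/SE − 1.96).

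Power of 98% needs |β|/SE = 1.96 + 2.054 = 4.014. Hence s² + 1/(m p(1−p)) may be at most 36 × (0.1625/4.014)² = 0.0590.

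| m per surgeon | p | 1/(m p(1−p)) | largest s² | largest s for 98% |
|---|---|---|---|---|
| 200 | 35% | 0.0220 | 0.0370 | 0.19 |
| 200 | 15% | 0.0392 | 0.0198 | 0.14 |
| 100 | 35% | 0.0440 | 0.0151 | 0.12 |
| 100 | 20% | 0.0625 | none | not reachable |
| 100 | 15% | 0.0784 | none | not reachable |

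For the last two rows the sampling term alone exceeds 0.0590. At m = 100, p = 15% and s = 0, power is about 94%.

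**Step 3. Power at other residual SDs.**

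| m | p | s = 0.2 | s = 0.3 | s = 0.4 |
|---|---|---|---|---|
| 200 | 35% | 97.5% | 83% | 63% |
| 200 | 15% | 93% | 77% | 59% |
| 100 | 35% | 92% | 76% | 58% |
| 100 | 15% | 81% | 66% | 51% |

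Example (m = 200, p = 35%, s = 0.3): SE = √[(0.09 + 0.0220)/36] = 0.0558; 0.1625/0.0558 − 1.96 = 0.95; Φ(0.95) = 83%.

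**Step 4. Effect of the count alone.** At p = 35%, take the s² of 0.0370 that gives 98% with 200 per surgeon. With 100 per surgeon, SE = √[(0.0370 + 0.0440)/36] = 0.0474, and power = Φ(0.1625/0.0474 − 1.96) = Φ(1.47), or 93%.

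**Step 5. Check of the approximation.** A simulated random-intercept logistic model (likelihood-ratio test, 400 runs per setting) with m = 200 and p = 35% gave 96%, 84% and 62% at s = 0.2, 0.3 and 0.4, in line with Step 3. Using a t reference with 34 degrees of freedom lowers the limits at m = 200 only slightly, to about 0.18 (35%) and 0.13 (15%).

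**The case against.** The strongest reply is that the slip is only a missing time unit. The total of 7200 appears in both power sections, the 2-year window is stated elsewhere, and 100 per year for 2 years gives 7200 exactly. This stands as the likelier explanation, so a reader should not infer that the true size is 3600. Nothing in the article shows that the simulation used 3600. If it did use 100 per surgeon and found 98%, then 7200 operations would give more than 98%. But the unit is not on the page, and both printed figures cannot be right over the same 2 years.

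A reader might also infer that 98% holds only if almost no surgeon or hospital variation remains after adjustment. The calculation does not support that:
- With 7200 operations at 35%, skill would explain 0.0264/(0.0264 + 0.0370) = 42% of between-surgeon variance (0.0264 = 0.1625²), leaving 58% unexplained.
- Modelled hospital variance costs little by itself. With 200 per surgeon, p = 35% and surgeon SD 0.2, a hospital SD of 0.4 lowers power from 97.5% to 95%, or to 88% if 30% of skill variance lies between hospitals. At surgeon SD 0.1, power stays at or above 98% in either case.

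Nor does the Aim 2 effect contradict the Aim 1 power. That argument needs an assumed event rate and an assumed correlation between technical and nontechnical skill. At 35% the residual SD it would add, about 0.14, is below the limit of 0.19.

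Finally, a journal article may leave event rate and variance inputs to a fuller document, so their absence is not in itself an error. The Analytical Plan includes surgeon and hospital random effects, and nothing shows that the simulation ignored clustering. What remains is the irreconcilable count and a single 98% that inherits its ambiguity.

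**Conclusion.** The figures in the Aim 1 Power Analysis are wrong as written and need reconciling, because the stated power rests on them and Aim 2 borrows the result. The 98% is attainable but not shown to be wrong or right. With 200 operations per surgeon it requires a residual surgeon SD of at most about 0.19 at an event rate of 35%, or 0.14 at 15%. With 100 per surgeon it requires at most about 0.12 at 35% and is out of reach at 20% or lower. Even with 7200 operations, a residual SD of 0.3 would bring power to about 83% or 77%.

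These results assume equal volumes per surgeon, skill measured without error, no loss of precision from covariates, and no hospital variance in the main tables. Each of these favours the stated power. The 15% and 20% event rates and the residual SDs are assumptions; the article gives no surgeon-level SD. The 35% is the article's general adverse-event figure and is not tied to the power calculation. The inconsistency in the count depends on none of these assumptions.

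**What to change.** 1. Establish which size the simulation used. Then either change the parenthesis to about 200 operations per surgeon over 2 years (100 per year), or change the total to 3600.
2. Confirm or restate the 98% for that size. Give it as a range over plausible residual surgeon SDs and event rates, not as a single figure. The sites' existing 2-year registry data could supply both inputs.
3. Carry the corrected size and power into the Aim 2 Power Analysis, which relies on the same figures.

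The cost is a check of the simulation inputs, possibly a re-run, and a few words of revised text. The stated power may become less favourable. No additional surgeons are needed.

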### Aim 2: Investigate the Relationship Between Peer-Rater Assessments of Intraoperative Team-Based Nontechnical Practices and Variability in Risk-Adjusted Patient Adverse Events

#### Approach

We will leverage each hospital’s intraoperative electronic health record system for video segmentation, using in part precomputed, validated, publicly available MPOG phenotypes [24,32]. Segments will be reviewed by at least 12 assessors (three per provider group). We will assess the association between peer assessments of nontechnical practices and surgeon measures of postoperative major morbidity and mortality, adjusted for patient risk factors and surgeon technical skills.

#### Measures

Our primary exposure will be the average summary peer assessment of each provider’s nontechnical practices. Similar to aim 1, the primary outcome will be the rate of major morbidity or mortality, adjusting for clinical covariates [30,31].

#### Analytical Plan

We will use generalized linear mixed effect models with a logit link to associate peer-assessor assessments of nontechnical practices of the surgeon with the surgeon’s STS composite score for major morbidity and mortality. Models will be similar to those described in aim 1, although we will include average summary measures of surgeon’s nontechnical skills as surgeon-level explanatory variables and hospital-level average summary measures of anesthesiologists, perfusionists, and scrub nurses. Both overall summary measures and individual scale domains will be considered. We will focus primarily on assessing the effects of nontechnical practices on morbidity and mortality rates, while adjusting for patient-level risk factors and a surgeon’s technical skills. We will explore the influence of nontechnical practices on the relationship between a surgeon’s technical skills and our composite endpoint by including nontechnical practices as an interaction term in models with technical skills.

#### Power Analysis

The power analysis is based on approximately 7200 cases across 36 surgeons from six hospitals. As surgeon’s nontechnical practices are considered a surgeon-level variable, there will be sufficient power in detecting the same effect sizes as reported in aim 1.

### Aim 3: Explore the Feasibility of Using Objective, Data-Driven, Computer-Based Assessments to Automate the Identification and Tracking of Significant Intraoperative Determinants of Risk-Adjusted Patient Adverse Events

High-dimensional computer-based assessments of digital recordings will be used to recognize and track human activity (computer vision). Computer vision focuses on training computers to derive meaning from visual imagery. Video understanding, a specialty within computer vision, focuses on identifying and tracking objects over time from video and developing mathematical models to train computers to extract the meaning within these moving images. This field may offer unparalleled capabilities for conducting objective peer assessments by automatically identifying and tracking human activity comparable to that of expert human assessors.

#### Background

##### Surgical Technical Skills

Video understanding may address some of the limitations in traditional mentored or simulation-based approaches for assessing a surgeon’s technical skills, including human assessor bias and limited scalability. Prior investigations have documented the reliability of video-based surgical motion analyses for assessing laparoscopic performance as compared to the traditional time-intensive human assessor approach [33,34]. Azari et al compared expert surgeon’s rating assessments to computer-based assessments of technical skills [35]. Computer-based assessments had less variance relative to expert assessors. Sarikaya et al evaluated the feasibility of computer-based methods for technical skill assessment involving 10 surgeons having varying experience with robotic-assisted surgery [36]. This evaluation included acquiring 99 unique videos with 22,467 total frames and the development of a state-of-the-art deep learning–based surgical tool tracking system. The quantitative assessment against gold standard (human annotated) tool tracks found a 90.7% mean average precision over all test videos across all surgeon skill levels.

##### Nontechnical Practices

Nontechnical practice assessments have predominantly occurred within simulated environments and relied on trained human observers [37,38]. Investigators have not evaluated whether video understanding could provide an objective alternative for high-fidelity assessments of nontechnical practices in real-world operative environments, generalizable across hospitals with varied operating room layouts and camera configurations. Video understanding may be used to assess features aligned with nontechnical practices without relying on verbal communication [39]. Video understanding requires time-limited human observer involvement to provide labels for training algorithms after which the automated system may be deployed at scale.

#### Approach

We will explore the feasibility of using a video-understanding platform to identify important features associated with assessor ratings in recorded operations. To support developing the video-understanding platform, we will conduct interviews and site visits at a subset of low- and high-performing hospitals to enhance the understanding of a hospital’s contextual characteristics (eg, culture) and important “usual practices.”

##### Video Understanding

The video-understanding approach will focus on two specific techniques (ie, visual detection and visual tracking), which will be applied to identify and measure surgeons’ technical skills (aim 1) and team-based nontechnical practices (aim 2). We will apply ambiguity reduction across the three time-synchronized video recordings to harmonize (rather than duplicate) *elements* within and across video angles. We will use proven methods for video understanding (eg, boosting [40] and deep learning [41]). We will use boosting for cases of limited data and deep learning for cases of ample data. We will learn detection models to ascertain kinematic features potentially associated with surgical technical skills (eg, path length of the surgeon’s suturing and nonsuturing hands) and nontechnical practices (eg, identifying and tracking the gaze direction of team members at critical times of the surgical procedure) based on aims 1 and 2. We will learn these features using the following mutually exclusive data sets containing video segments: (1) training data set (used for training the video-understanding algorithms); (2) computer vision validation data set (used to mitigate risk of overfitting [eg, the video-understanding algorithms]); (3) computer vision testing data set (used for computing the error statistics of the computer vision system to meet human feature annotation); and (4) study set (video segments for peer assessments). Investigators will observe the raw video from the training data set to provide bounding-box annotations for each feature, within contextual feedback provided by members of the investigative team who work in the operating room. A certain detection model is initialized with a random set of parameters, and then, the training algorithm iteratively refines them based on the model’s empirical performance (ability to automatically detect the phenomena bounding boxes) based on the annotations in the training data. The validation set is used during this training process to protect against overtraining and bias. Some technical assessments will require detection in a video frame and tracking of the detected object throughout the video frames (“visual tracking”). For example, to measure the surgeon’s economy of motion, we will detect the surgeon’s hands at frame t, track the surgeon’s hands at all future frames t+k, and then compute a trajectory of the centroid of the detected bounding boxes. We will use both classical physics-based tracking models (eg, Lucas-Kanade tracking [42]) and modern deep learning–based methods [43]. We will compute a range of validated kinematic features [35] and quantifiers of economy of motion (eg, path length of the surgeon’s suturing and nonsuturing hands, and variance of local change in the trajectory against a linear or smoothed trajectory).

##### Qualitative Interviews

Concurrent with developing and testing the video-understanding platform, we will randomly select up to four of the six hospitals (equal representation of low- and high-outlier hospitals) participating in aim 2 for more detailed investigation. We will conduct semistructured interviews with interdisciplinary cardiac surgery operating room team members. To enhance our understanding of technical and nontechnical operating room practices, we will collect data (through interviews with intraoperative team members) concurrent with conducting analyses. We will develop a semistructured interview guide to encourage new and/or unexpected ideas or concepts to surface. For each interview, the interviewer will play back video segments from an operation involving the interviewee and ask the interviewee to describe his/her role within that operative phase. The interviewer will ask questions seeking to better understand team member roles and influences on technical skills and nontechnical practices. We expect the guide will consist of seven to nine open-ended questions with probes. Interviewers will participate in a 3-day training program at the University of Michigan Health Communications Laboratory. Interviews will continue until reaching informational redundancy “saturation” at each hospital. We will (1) conduct 40 to 60-minute interviews in private rooms, (2) digitally record and transcribe transcripts verbatim, (3) compare 10% of transcripts (and correct as needed) against the recordings, and (4) provide interviewees with a gift certificate. We expect that (1) in reviewing the videos, providers will complement peer assessments regarding how and why contextual factors influence performance (technical and nontechnical) and (2) interviewees will validate the video content to maximize our video understanding algorithm’s fidelity. Thus, our interview findings will improve our interpretation of the video content to iteratively inform and enhance our video-understanding platform’s training.

#### Measures

Our primary outcome will be the features derived from the video-understanding platform, which will be compared to a gold standard human identifying the same features. Features, as economy of motion, are derived from the raw output of the video-understanding platform, which naturally performs visual detection and visual tracking. The gold standard uses the analogous “raw output” from humans and the same method for the computation of the derived feature.

#### Analytical Plan

We will assess our video-understanding platform’s ability to correctly identify and track features within our testing data set. Using the raw video in the testing set, we will provide the necessary bounding-box annotations for each feature, which will be compared to the automatically generated features from the video-understanding system using standard metrics (eg, intersection over union [44] and DICE coefficient [45]). For example, when we compute the economy of motion of the surgeon’s hand, we will provide bounding-box annotations of the surgeon’s hand. The video-understanding system will use these annotations to learn a mathematical visual detection model capable of producing the detections of the hand on novel video. Thereafter, the economy of motion feature will be derived on the output bounding boxes. We plan a two-phased analysis. First, we will measure agreement and associate each feature with each component of the technical and nontechnical assessments (specific to each operative phase) using Pearson/Spearman correlation coefficients or Kendall tau, depending on data distribution. Second, we will identify the best combination of video-understanding features that are most closely associated with technical and nontechnical score domains (specific to each operative phase). We will use regression (eg, linear, ridge, and deep) to model each domain and technical and nontechnical summary scores as dependent variables, including features from the video-understanding platform as independent variables. We will (1) select features using variable selection and (2) quantify the magnitude of information in peer assessment that can be identified by the computer using generalized R squares.

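### Aim 3 makes derived features the primary outcome, but the only platform-versus-human metrics it names score box overlap, which does not measure agreement in features such as path length

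*Protocol article*

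**What the plan says.** The Aim 3 Measures section states: "Our primary outcome will be the features derived from the video-understanding platform". It separates the platform's raw output (detection and tracking) from the feature derived from it, with economy of motion as the example. The gold standard is human raw output put through "the same method for the computation of the derived feature". As defined there, the primary comparison is therefore at feature level.

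The Video Understanding section gives examples of economy-of-motion quantities: "path length of the surgeon’s suturing and nonsuturing hands, and variance of local change in the trajectory". They come from a track, since the plan will "compute a trajectory of the centroid of the detected bounding boxes".

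The Aim 3 Analytical Plan describes the platform-versus-human step on the testing set. Human bounding-box annotations are made and are to be "compared to the automatically generated features from the video-understanding system using standard metrics (eg, intersection over union [44] and DICE coefficient [45"). After that, "the economy of motion feature will be derived on the output bounding boxes". The correlations and regressions that follow relate features to components and domains of the peer assessments.

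**The concern.** The outcome and the metrics named for it sit at different levels. IoU and DICE ask, frame by frame, how well two boxes coincide. Path length adds up the centroid's moves from one frame to the next. Small errors that barely affect overlap can accumulate in that sum, while a steady displacement of the box, which costs much overlap, leaves the sum unchanged.

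If overlap were the only accuracy result reported, a reader would learn how well the platform finds hands. The reader would not learn how well it reproduces the human-derived feature, which is the comparison called primary. The same features then enter the correlations with peer scores and the generalized R-square. A weak association there could mean that the feature was badly measured or that assessors judge something else. Without feature-level agreement the two cannot be told apart.

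**Working it through.** **Plan's own figure.** The article gives no numeric target for Aim 3 (no overlap threshold, agreement target or number of test segments), so there is nothing to reproduce.

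**Inputs, all assumed.** Hand box 120 × 120 px; 30 frames/s; Gaussian error in the box centre with SD s = 4 px per axis; true speed 60 px/s, so v = 60/30 = 2 px per frame. Speed, s and the lag-1 correlation ρ of the error are varied.

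**Overlap.** For equal boxes of width w displaced by (dx, dy), the intersection is i = (w − |dx|)(w − |dy|), IoU = i/(2w² − i), and DICE = 2·IoU/(1 + IoU).
- s = 4 px: mean IoU 0.90, DICE 0.95.
- s = 2 px: mean IoU 0.95.

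DICE is a fixed function of IoU for a given pair of boxes, so naming both does not widen what is measured.

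**Path length.** The measured step is the true step plus noise with per-axis SD σ = s·√(2(1 − ρ)). Its mean length is σ·√(π/2)·L(−v²/(2σ²)), where L is the Laguerre function of order ½. Dividing by v gives the ratio of measured to true path length.

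Worked case, ρ = 0: σ = 4·√2 = 5.66; v²/(2σ²) = 4/64 = 0.0625; L ≈ 1.031; mean step = 5.66 × 1.253 × 1.031 ≈ 7.31 px; ratio = 7.31/2 ≈ 3.65. A direct simulation of 18,000 frames gives 3.6 to 3.7.

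| Lag-1 correlation ρ (s = 4 px, IoU about 0.90) | Ratio at 60 px/s | Ratio at 120 px/s |
|---|---|---|
| 0 | 3.65 | 1.99 |
| 0.8 | 1.82 | 1.22 |
| 0.9 | 1.45 | 1.11 |
| 0.95 | 1.22 | 1.05 |
| 0.99 | 1.04 | 1.01 |

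Every row has the same per-frame overlap, so overlap cannot tell these cases apart.

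**Other conditions.**
- Faster hand, 240 px/s, ρ = 0, s = 4 px: ratio 1.28.
- Less jitter, s = 2 px, 60 px/s, ρ = 0: ratio 1.99.
- Human boxes with half the jitter (2 px), both independent, 60 px/s: platform/human ratio 1.84, with IoU between the two sets of boxes 0.89. At 240 px/s the ratio is 1.20.
- Human boxes with equal jitter: platform/human ratio about 1.0, because both paths are inflated alike.
- 15-frame moving average, 60 px/s, ρ = 0, s = 4 px: ratio falls from 3.6 to 1.02.

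**Converse.** For a constant offset of 40 px on each axis, the overlap region is 80 × 80 px. IoU = 6400/(2 × 14400 − 6400) = 6400/22400 = 0.29. Every frame-to-frame move is unchanged, so path length is exactly right.

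**The case against.** Four points on the other side carry weight.

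- **The intent to compare features is stated.** The Measures section says the platform's features will be compared with a human standard for the same features, computed alike. A reader might infer that no feature-level comparison is planned. The article does not support that. It supports only that the metrics named do not measure that comparison.
- **The overlap sentence concerns boxes, and its list is open.** Its subject is bounding-box annotations, for which IoU and DICE are suitable, and the two are introduced as examples. This stands. It does not close the gap, because both examples are overlap scores and the only other coefficients in the section relate features to peer scores. The word agreement does appear beside those coefficients, but a correlation would in any case miss a proportional inflation.
- **The large ratios rest on a harsh noise model.** Independent jitter treats each frame as detected afresh. The plan describes detecting the hands once and then tracking them, which plausibly makes errors correlated over time. The human track also has error. Both reduce the ratio substantially, as the table shows.
- **The consequence is limited.** Aim 3 is feasibility work, and no threshold is set at which the platform would be declared equivalent to humans. If jitter is the same in all segments of equal length, the ordering by path length is kept on average and rank correlations change little. Other features, such as gaze direction, were not examined here.

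A condensed article may leave the exact agreement statistic to a fuller document, and an unnamed statistic alone would be no fault. The point here is narrower: the metrics that are named do not fit the outcome that is named.

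**Conclusion.** The mismatch holds and does not depend on any assumed number. The primary outcome is the derived feature, and the metrics stated for platform versus human measure box overlap, which is neither sufficient nor necessary for a correct path length.

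The size is uncertain. At an IoU of about 0.90 and 60 px/s, path length is between about 1.04 and 3.7 times true as the error goes from strongly correlated to independent. Against human boxes with half the independent jitter the ratio is about 1.8. It is near 1 with equal jitter or smoothing, and approaches 1 as motion gets faster. Box size, frame rate, speed and jitter are all assumptions.

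A reader might infer that the platform's path length will be several-fold wrong, or that the platform would be passed as matching humans on overlap alone. The article supports neither: it gives no error properties for the tracker and no pass mark. What follows is that the stated metrics could not reveal such an error if it occurred.

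**What to change.** Keep IoU or DICE, labelled as the check of raw detection. For the primary outcome, add to the Aim 3 Analytical Plan that each derived feature will be computed from the automated track and from the human-annotated track on the same test segments, and that feature-level agreement will be reported as bias with limits of agreement and an absolute-agreement ICC. Fix the frame sampling and any trajectory smoothing in advance, and apply them identically to both tracks before path length is computed. Smoothing appears in the article only as a reference for the separate trajectory-variance feature, so its use for path length needs stating.

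The cost is a change of wording and a small extra analysis on annotations and tracks already planned. Reported platform accuracy may look less favourable than overlap scores alone.
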